**Methods:**

In this prospective study (NCT05868928), patients with brain metastases will undergo multi-parametric MRI before SRS, and then follow-up MRIs will be conducted every 3 months until 24 months after SRS. The multi-parametric MRI protocol will include T2-weighted and contrast-enhanced T1-weighted imaging, diffusion-weighted imaging, and dynamic susceptibility contrast imaging. Using k-means voxel-wise clustering, this study will define three structural MRI habitats (enhancing, solid low-enhancing, and nonviable) on T1- and T2-weighted images and three physiologic MRI habitats (hypervascular cellular, hypovascular cellular, and nonviable) on apparent diffusion coefficient maps and cerebral blood volume maps. Using RANO-BM criteria as the reference standard, via Cox proportional hazards analysis, the study will prospectively evaluate associations between parameters of the tumor habitats and the time to recurrence. The DICE similarity coefficients between the recurrence site and tumor habitats will be calculated.

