#### Secondary objectives

To match the site of tumor recurrence with each tumor habitat.To measure the per lesion–based response.To evaluate the occurrence rate of RN, which will be determined through a combination of follow-up MRI findings and clinical evaluation by a multidisciplinary team.

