### Tumor habitat analysis

Tumor habitat analysis will be performed at baseline and for every follow-up MRI scan.

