#### Progressive disease

Progressive disease is defined as at least a 20% increase in the sum of the longest diameters of the target lesions, taking as reference the smallest sum in the study (this includes the baseline sum if that is the smallest in the study). In addition to a relative increase of 20%, at least one lesion must grow by an absolute value of 5 mm or more to be considered as progression. When there are mixed signs of progression and RN, the response assessment will continue to adhere to the RANO-BM criteria, as described. If lesions grow according to the definition of “progressive disease,” they will be classified accordingly.

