#### RN

The reference standard of RN or tumor progression will be diagnosed according to the clinicoradiological consensus of a multidisciplinary team including two neuroradiologists ([name] and [name], with 10 and 25 years of experience in neuro-oncologic imaging, respectively), two neurosurgeons ([name] and [name], with 20 years and 23 years of experience, respectively) and a neuro-oncologist ([name] with 13 years of experience). The multidisciplinary team will review all imaging and medical records. RN will be diagnosed when there is an increase in the contrast-enhancing lesion size and it subsequently regresses or becomes stable without any change in treatment at least 6 months after SRS, and when there are progressive neurological signs corresponding to the location of the RN [16, 17]. Additional imaging modalities, such as positron emission tomography or single-photon emission tomography, may be used along with MRI if deemed clinically necessary and will be considered during the multidisciplinary discussions for diagnosing RN.

Additionally, when such a lesion yields a symptomatic mass effect, a second-look operation is justified to confirm the pathological diagnosis. Expert neuropathologists in our hospital will review the lesion specimens to determine whether the findings indicate RN or tumor progression when surgical resection is performed. RN will be diagnosed as described in previous literature, characterized by an area of necrosis that appears hypocellular and is sharply demarcated from the surrounding gliotic brain, with necrotic, hyalinized blood vessels [18–20]. When histologic features of both RN and tumor progression are present in specimens, those composed of more than 25% tumor cells will be defined as recurrent tumors, whereas those with less than 25% tumor cells will be classified as RN [21].

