### Statistical analysis

Analysis of the association between the tumor habitats and time to recurrence will be conducted using Cox proportional hazards regression analysis. The imaging predictor exhibiting a strong association will be selected on the basis of both univariate and multivariable Cox proportional regression analysis. Adjustments for time-dependent covariates will be made.

The prediction model for time to recurrence will be created by combining imaging predictors and clinical variables. The performance of the prediction model will be analyzed using C-statistics and time-dependent receiver operating characteristic curve analysis, and calibration (Hosmer-Lemeshow goodness-of-fit test) will be evaluated.

The Dice similarity coefficient will be calculated when the recurrence is diagnosed. The area of each habitat before SRS will be divided by the contrast-enhancing lesion at the time of tumor recurrence.

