## Discussion

This study aims to prospectively evaluate a tumor habitat-based imaging biomarker to predict tumor recurrence in SRS-treated BM. Tumor habitat analysis will be conducted using baseline multi-parametric MR images and follow-up MR images captured after SRS treatment. Metastatic tumors are biologically complex and exhibit significant spatial variation in their structural properties. This intratumoral and peritumoral heterogeneity becomes even more complex after SRS, when it becomes combined with radiation-induced changes. The grouping of voxels of similar signal intensity may enable identification of subregions that share common biologic characteristics and respond differently to treatment, providing information that may not be detectable through visual analysis.

A previous autopsy study indicated that the enhancing areas of post-SRS lesions consist of various pathologic components, including viable tumor tissue, necrotic tissue, inflammatory cells, and vessels [22]. The degree of enhancement cannot differentiate between these complex components, and analyses relying solely on enhancing lesions cannot distinguish progression and radiation-induced changes. Previous studies have demonstrated the predictive value of the correspondence or proportion of solid lesions on T2WI and enhancing lesions on CE-T1WI for diagnosing viable tumors [23, 24]. Interval decreases in the ADC or rCBV values of treated lesions have also been reported to indicate tumor responses following SRS [25–28]. However, visual assessment of structural MRI is limited in terms of reproducibility and its inherent subjectivity. Furthermore, a single quantitative parameter may fail to provide a thorough explanation of the intricate tumor biology mixed with RN. Thus, in this study, we will use CE-T1WI and T2WI for the structural tumor habitat analysis, and ADC and CBV maps for the physiologic tumor habitat analysis. The prospective longitudinal analysis of tumor habitats will enable us to track changes across different subregions in fine detail.

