The imaging biomarker developed in this prospective study will provide an objective and reliable measure for assessing tumor recurrence following SRS. Identification of the subregions at increased risk of recurrence will facilitate the establishment of an optimal strategy for close monitoring of therapeutic targets and distinguishing nonviable tumor areas that can be considered safe for observation. Such an accurate imaging assessment of tumor progression or radiation-induced change will help avoid unnecessary surgery or radiation therapy, thereby minimizing associated patient morbidity.

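### Matching the recurrence site to pre-SRS habitats by raw Dice, with no reference for habitat volume, confounds location with habitat size

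*Protocol article*

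**What the plan says.** The first secondary objective is "To match the site of tumor recurrence with each tumor habitat". The Abstract (Methods) names the measure: "The DICE similarity coefficients between the recurrence site and tumor habitats will be calculated". The Statistical analysis section then fixes the two regions: "The area of each habitat before SRS will be divided by the contrast-enhancing lesion at the time of tumor recurrence". The habitats are therefore those on the pre-SRS scan, and the recurrence site is the entire enhancing lesion. The article gives no expected or chance level of overlap for comparison.

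Four other places bear on this:

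- Tumor habitat analysis: "Tumor habitat analysis will be performed at baseline and for every follow-up MRI scan".
- Progressive disease: growth is judged "taking as reference the smallest sum in the study", and lesions with mixed signs of progression and radiation necrosis (RN) are still classified by size.
- RN: of resected specimens with both features, "those composed of more than 25% tumor cells will be defined as recurrent tumors".
- Discussion: "analyses relying solely on enhancing lesions cannot distinguish progression and radiation-induced changes". The intended use is also stated there: "Identification of the subregions at increased risk of recurrence will facilitate the establishment of an optimal strategy for close monitoring of therapeutic targets".

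**The concern.** The habitats divide one lesion into three parts of unequal volume. A large part overlaps more with almost anything in the same place than a small part does. Without a reference for volume, a habitat can look linked to recurrence because it is large, or look safe because it is small.

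The comparison region adds a second difficulty. By the Discussion's own account, the enhancing lesion after SRS mixes viable tumor with treatment effect. Part of what is called the recurrence site may therefore not be recurrence.

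At stake are the first secondary objective and the claims built on it: subregions at risk, next therapeutic targets, and nonviable areas that can safely be observed.

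The sentence in Statistical analysis also describes a ratio of areas with no intersection term. That is a separate matter. The point here remains once the intersection is put in.

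**Working it through.** The plan states no figure for the overlap, so there is none to reproduce. The check asks what a correct Dice would show.

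**Notation.** Baseline lesion volume = 1; H = habitat volume, with share f of the baseline lesion; L = recurrent lesion volume. Dice = 2|H∩L| / (|H| + |L|). The protocol gives no habitat shares or lesion sizes, so those below are assumptions.

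**1. No link, recurrent lesion inside the baseline outline (volume v).** The expected intersection is f × v, so expected Dice is about 2fv/(f + v). This rises with f for every v. At v = 0.6:

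| Share f | Calculation | Dice |
|---|---|---|
| 0.2 | 0.24/0.80 | 0.30 |
| 0.3 | 0.36/0.90 | 0.40 |
| 0.5 | 0.60/1.10 | 0.545 |

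**2. Recurrent lesion covers the baseline lesion.** The intersection is the habitat itself, so Dice = 2H/(H + L) and the ranking follows size alone. For shares 50/30/20%:

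| L (× baseline) | 50% | 30% | 20% |
|---|---|---|---|
| 1.0 | 0.667 | 0.462 | 0.333 |
| 2.0 | 0.400 | 0.261 | 0.182 |
| 3.0 | 0.286 | 0.182 | 0.125 |

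**3. Recurrence with a known origin.** A voxel model used a sphere of radius 1 cut into habitats A, B and C holding 48%, 25% and 26%, with a spherical recurrence centred in one of them. Dice for A/B/C:

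| Radius | Origin A | Origin B | Origin C |
|---|---|---|---|
| 0.6 | 0.573/0.026/0.000 | 0.165/0.388/0.281 | 0.000/0.120/0.608 |
| 0.8 | 0.710/0.142/0.000 | 0.333/0.430/0.470 | 0.017/0.261/0.586 |
| 1.0 | 0.625/0.238/0.034 | 0.481/0.402/0.418 | 0.095/0.310/0.419 |
| 1.8 | 0.152/0.083/0.087 | 0.152/0.083/0.087 | 0.152/0.083/0.087 |

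At radius 0.6 the true origin ranks first every time. At 0.8 it fails for origin B. At 1.0 a recurrence from B puts A, the largest habitat, first. At 1.8 the three origins cannot be told apart.

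**4. What a volume reference changes.** Take the ratio (fraction of habitat covered) / (fraction of whole pre-SRS lesion covered).

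- Case 1: 0.6/0.6 = 1 for every habitat, as it should be with no link.
- Case 2: 1/1 = 1 for every habitat, which correctly signals no information on origin.
- Origin B at radius 1.0: the fraction covered is Dice × (H + L)/(2H). With L = 1.00 this is 0.481 × 1.481/0.962 = 0.74 for A, 0.402 × 1.254/0.508 = 0.99 for B and 0.418 × 1.265/0.530 = 1.00 for C. The whole lesion is covered to 0.481 × 0.74 + 0.254 × 0.99 + 0.265 × 1.00 = 0.87. The ratios are 0.85, 1.14 and 1.14, so A no longer ranks first. B and C remain tied: the ratio removes the size effect but does not recover the origin of a large recurrence.

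**The case against.** A reader might infer that the planned overlap cannot show origin at all, or that habitat size alone sets the ranking. The documents and the arithmetic do not support that. The formula in step 1 is a chance level and does not describe what Dice shows when a link exists. With shares 20/30/50% and L = 0.6, suppose the recurrence takes all of the two smaller habitats and 0.1 of the largest. Dice is then 0.4/0.8 = 0.50, 0.6/0.9 = 0.67 and 0.2/1.1 = 0.18, so the largest habitat ranks last. This objection stands. Even so, the two fully covered habitats differ (0.50 against 0.67) only through their size, whereas their ratios are equal at 1/0.6 = 1.67.

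A reader might also infer that the pre-SRS map is the wrong time point, since habitats are mapped at every follow-up. That does not hold either. Whether a pre-treatment subregion predicts where recurrence appears is a legitimate question for a study of prediction, and the objective promises only a match. Nor do the documents say that lesions typically shrink before regrowing; the Progressive disease section allows baseline to be the smallest sum.

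The apparent remedy of overlapping new growth with habitats on the last scan before progression largely fails. The section on segmentation and image processing confines habitats to the enhancing lesion, so growth outside that lesion has zero overlap with that scan's habitats by construction.

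Finally, the analysis is secondary and descriptive. That limits how much weight the point deserves, but does not remove it.

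**Conclusion.** The point holds in limited form and is a cheap improvement. Raw Dice against the whole enhancing lesion is confounded by habitat size even when computed correctly. Under no link it runs from 0.30 to 0.545 across shares of 20% to 50% at v = 0.6, and it ranks by size alone once the recurrence covers the baseline lesion. It does carry location information for focal recurrences. It therefore does not reliably identify the habitat of origin, and it is a weak basis for the subregion and target claims.

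The rise with habitat size is algebra. The particular values rest on assumed shares, spherical geometry and perfect registration, and how often recurrences will be focal is unknown. The mixing of tumor and radiation change within the enhancing lesion is a further limit, which a volume reference does not remove. The primary Cox analysis is unaffected.

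**What to change.** In Statistical analysis, keep the pre-SRS habitat map and make these changes:

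- Compute the true spatial intersection of each habitat with the registered lesion at recurrence.
- Alongside Dice, report for each habitat the fraction covered by the recurrent lesion divided by the fraction of the whole pre-SRS lesion covered. A value of 1 is what habitat volume alone predicts.
- Count separately the lesions whose recurrence covers the whole baseline lesion (ratio 1 for every habitat), and treat them as uninformative about origin.
- Optionally, as a sensitivity analysis, overlap the growth since nadir with the pre-SRS habitats. Do not overlap growth outside the last pre-progression lesion with that scan's habitats.
- State that the enhancing lesion may include radiation change, and word the conclusions on subregions accordingly.

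The cost is some extra image analysis on scans already planned, a less favourable-looking overlap figure, and sensitivity to registration error, since registration is rigid and does not model shrinkage or growth. No new scans are needed.

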#### Deep learning segmentation and image processing

Brain extraction and deep learning segmentation will be performed on FLAIR and 3D CE-T1WI using an algorithm (https://github.com/MIC-DKFZ/nnUNet) in the PyTorch package (version 1.1) in Python 3.7. The segmentation of contrast-enhancing lesions, defined as the contrast-enhancing solid portions on CE-T1WI, will be performed and included in the tumor habitat analysis. Lesions showing similar high-signal intensity on both pre-contrast T1WI and CE-T1WI will be considered as hemorrhagic lesions and excluded from the analysis. This process will be supervised by an experienced neuroradiologist ([name], with 10 years of experience).

The signal intensities of the T2WI and CE-T1WI will be normalized using the kernel density estimation–based white matter segmentation tool [13] in R (R Foundation for Statistical Computing, Vienna, Austria). A pharmacokinetic map will be computed using Nordic ICE software (NordicNeuroLab) for analysis of DSC. The blood quantity will be measured through an integrated DSC module, which combines a leakage correction algorithm for the relative CBV (rCBV) with manual noise thresholding. To generate normalized CBV (nCBV) maps, the rCBV maps will be adjusted to align them with the levels found in normal white matter.

To evaluate the changes on follow-up MRI, the 3D CE-T1WI of the patient will be co-registered and resampled into isometric voxels. The T2WI, nCBV, and ADC images will also be co-registered and resampled into the same space as the isovoxel CE-T1WI images using rigid transformations with six degrees of freedom in the SPM package (version 12; https://www.fil.ion.ucl.ac.uk/spm/).

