### Sample size calculation

The sample size for this prospective study was determined according to binomial receiver operating characteristic curve analysis performed in diagnostic accuracy studies by a biostatistician ([name], with 12 years of experience). The sample size was calculated using PASS 15 Power Analysis and Sample Size (NCSS, Kaysville, Utah, ncss.com/software/pass). The null hypothesis of an area under the curve (AUC) of 0.7 was compared with an alternative hypothesis of an AUC of 0.85 for the tumor habitat analysis for the determination of RN. The target distribution was the rate of RN versus tumor recurrence, which is known to be detected in a 1:2 ratio in post-treatment BM [4]. With an alpha of 0.05 (type-1 error) and a beta of 0.20 (type-2 error), 34 positive cases (RN) and 68 negative cases (tumor recurrence), giving a total of 102 cases, were identified as the appropriate sample size. Considering a dropout rate of 10% and a censoring rate of 20% for BM, 132 patients were found to be appropriate for the study design.

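### The only calculation given for the Dice coefficient divides habitat size by recurrent-lesion size and has no overlap term, so read literally it cannot match recurrence site to habitat

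*Protocol article*

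**What the plan says.** Four places in the protocol article bear on this point.

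- Secondary objectives, first item: "To match the site of tumor recurrence with each tumor habitat". This is a question about location.
- Abstract, Methods: "The DICE similarity coefficients between the recurrence site and tumor habitats will be calculated". Two regions are compared, and no formula is given.
- Statistical analysis, last paragraph: "The Dice similarity coefficient will be calculated when the recurrence is diagnosed". The next sentence, which closes the section, is the only description of a calculation: "The area of each habitat before SRS will be divided by the contrast-enhancing lesion at the time of tumor recurrence".
- Deep learning segmentation and image processing: "To evaluate the changes on follow-up MRI, the 3D CE-T1WI of the patient will be co-registered and resampled into isometric voxels". The T2-weighted, blood-volume and diffusion maps are brought into the same space.

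No intersection of habitat and recurrence is mentioned anywhere in the article.

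**The concern.** Dice measures spatial agreement, and its numerator is the overlap of two regions. The calculation sentence puts the whole habitat in the numerator and the whole recurrent lesion in the denominator. An analyst who followed it would report a number that says nothing about where the tumor came back.

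The secondary objective on matching sites has no other analysis described for it. The Discussion builds on the spatial result: "Identification of the subregions at increased risk of recurrence will facilitate the establishment of an optimal strategy". If the formula is left open until recurrences have been mapped, at least three quantities are candidates (H/R, overlap divided by R, and Dice). They can give different answers about which habitat recurred, and the choice could then be made with the data in view.

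**Working it through.** **Inputs.** The article gives no habitat or lesion volumes and no expected Dice value, so there is no figure to reproduce. All sizes below are assumptions chosen to show how the quantities behave. H is the pre-SRS habitat, R is the enhancing lesion at recurrence, and H∩R is their overlap.

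**Formulas.**
- As written (Statistical analysis): H/R.
- Dice: 2|H∩R| / (|H| + |R|), which lies between 0 and 1.

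**Step 1: dependence on location.** Take H = 2 and R = 4. The written ratio is 2/4 = 0.50 in every position.
- Regions apart: Dice = 2×0/(2+4) = 0.
- Habitat wholly inside the recurrence: Dice = 2×2/(2+4) = 0.67.

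The same comparison over other assumed sizes, in voxels:

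| H | R | H/R at any overlap | Dice, no overlap | Dice, half of the smaller region | Dice, full overlap |
|---|---|---|---|---|---|
| 300 | 1000 | 0.30 | 0 | 0.23 | 0.46 |
| 300 | 600 | 0.50 | 0 | 0.33 | 0.67 |
| 300 | 300 | 1.00 | 0 | 0.50 | 1.00 |
| 300 | 150 | 2.00 | 0 | 0.33 | 0.67 |

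**Step 2: range.** The last row gives 2.00, which Dice cannot take. It requires a recurrence smaller than one baseline habitat. That is possible after shrinkage, because the Progressive disease section measures growth from the smallest sum of diameters in the study.

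**Step 3: ranking within a lesion.** R is the same for all habitats of a lesion, so H/R ranks them by H. Take baseline habitats of 500, 300 and 200 voxels and a recurrence of 200 voxels. The written ratios are 500/200 = 2.5, 300/200 = 1.5 and 200/200 = 1.0, wherever the recurrence lies.
- Recurrence wholly in the third habitat: Dice = 0, 0 and 2×200/(200+200) = 1.0.
- Recurrence wholly in the second habitat: Dice = 0, 2×200/(300+200) = 0.8 and 0.

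In both cases the ratio puts the 500-voxel habitat first, although its overlap is zero.

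**Step 4: when the two agree.** If every habitat lies inside the recurrence, |H∩R| = H and Dice = 2H/(H+R), which rises with H just as H/R does. With the same habitats and a recurrence covering exactly the baseline lesion (500+300+200 = 1000), H/R is 0.50, 0.30 and 0.20. Dice is 1000/1500 = 0.67, 600/1300 = 0.46 and 400/1200 = 0.33. The values differ but the order is the same. Outside this nested case the order under Dice depends on location, and agreement is not assured.

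**Step 5: Dice also depends on habitat size.** Let the 200-voxel recurrence lie half (100) in the first habitat and half (100) in the third. Each holds 100/200 = 0.50 of the recurrence, but Dice is 200/(500+200) = 0.29 for the first and 200/(200+200) = 0.50 for the third. Dice alone therefore does not report the share of the recurrence that lies in each habitat.

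**The case against.** The strongest reply is that the article never says Dice is defined as this ratio. It names a statistic with a standard overlap definition, in the Abstract and again in the Statistical analysis section, and a separate sentence about a division follows. That sentence may be loose wording for overlap divided by lesion, or an additional measure. A condensed article need not print the Dice formula at all. This stands: a reader might infer that the investigators have redefined Dice, and the text does not show that. Neither milder reading rescues the sentence, however. Overlap divided by lesion is still not Dice, and a separate size ratio would still say nothing about site. Nor can the point be left to a later analysis plan, because the protocol does state a calculation, and a plan would have to repeat it or contradict it.

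A second reply is that the same target lesion is followed over time and habitats are subregions of it, so a recurrence that engulfs the baseline lesion gives the same ranking under either formula. This also stands, but only for that case.

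Two further inferences should not be drawn. A reader might conclude that the claim to identify at-risk subregions would rest on a size ratio alone. It would not, because habitat parameters are also tested against time to recurrence by Cox regression. A reader might also take the word area to mean a two-dimensional measurement. The article uses that word loosely for tissue regions elsewhere and plans isometric-voxel processing.

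**Conclusion.** The sentence is wrong as a description of the statistic named immediately before it and should be corrected. Read literally, it gives a quantity that is blind to location, is not bounded by 1 and ranks habitats by baseline size, so it cannot answer the matching objective. In the assumed H = 2, R = 4 case, one value of 0.50 covers true Dice values from 0 to 0.67. The size of the error in practice depends on how recurrences sit relative to the baseline habitats, and the article gives no data on this.

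The conclusion rests on reading the division as the calculation for Dice, or at least as the only calculation offered for the matching objective. A drafting slip is the likely cause.

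The reach is limited to a secondary objective. The primary outcome is time to recurrence, and the sample size was set on a different quantity ("The null hypothesis of an area under the curve (AUC) of 0.7 was compared with an alternative hypothesis of an AUC of 0.85"). No hypothesis test or decision rule is attached to the Dice result.

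**What to change.** Replace the division sentence with: Dice = 2|H∩R| / (|H| + |R|), where H is the pre-SRS habitat mask and R is the enhancing-lesion mask at recurrence, both on the co-registered isometric voxels.

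If the share of the recurrence arising in each habitat is also of interest, name it separately as |H∩R|/|R|. It is best shown beside that habitat's share of the baseline lesion, because Dice itself varies with habitat size. This second measure is optional and is not needed to correct the error.

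The cost is one sentence. Segmentation, habitat maps and co-registration are already planned, so no new imaging, patients or sample size work is needed. I read the co-registration as aligning follow-up scans with baseline, which its stated purpose implies. The change should be made before any recurrence is mapped to a habitat.
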